**Fig. 1 Fig1:**
[figure not shown]
CONSORT diagram of the flow of participants throughout the research process

### Blinding

The therapist responsible for administering the intervention could not be blinded to treatment allocation because knowledge of the device setting was necessary to deliver either active photobiomodulation or sham photobiomodulation according to the study protocol. To minimize potential performance bias, the therapist followed a standardized intervention protocol, with identical patient positioning, application procedures, treatment duration, and interaction with participants in both groups. The sham intervention reproduced the same procedures as the active intervention, except for the absence of therapeutic light emission.

The therapist was not involved in outcome assessment or data analysis. Participants were blinded to treatment allocation through the use of fully occlusive protective goggles, which prevented the perception of light emission. Neither the active nor sham intervention produced a sensation of heat. Outcome assessors and data analysts also remained blinded to group allocation. At the end of the intervention, participants were asked to indicate which treatment they believed they had received, allowing assessment of the success of participant blinding by comparing their perceived allocation with their actual treatment allocation.

Unblinding occurred only in the event of a serious adverse event or when knowledge of treatment allocation was required for clinical decision-making and was performed by an independent researcher who was not involved in outcome assessment or data analysis.

### Intervention

The study will comprise two groups: (G1) photobiomodulation (PBM) and (G2) sham PBM, with both groups receiving usual postpartum care. Women diagnosed with first- and/or second-degree perineal trauma and/or obstetric vulvar edema will be invited to participate and randomly assigned to one of the two study groups.

A single treatment session will be performed during the immediate postpartum period, within 12 h after childbirth, with an approximate duration of 20 min. Before the intervention, participants will undergo the baseline assessment, including evaluation of perineal pain using the Numeric Rating Scale (NRS). In both groups, participants will receive individualized care and standardized education regarding pelvic floor anatomy, perineal trauma, vulvar edema, and perineal care. At the end of the immediate postpartum assessment, all participants will receive an educational leaflet containing recommendations for perineal care.

Participants allocated to G1 will receive PBM using the TERAPY-EC^®^ device with a wavelength of 808 nm (infrared), output power of 100 mW, beam area of 1 mm², and power density of 1.02 W/cm².

For participants presenting with first- and/or second-degree perineal trauma and pain ≥ 3 on the NRS, infrared light (808 nm) will be applied using a point-by-point technique, with an energy density of 60 J/cm² for 60 s per application point, corresponding to 6 J of energy per point. The irradiation will be performed around the perineal lesion and along the course of the pudendal nerve. One or two irradiation points will be used according to the size and extent of the lesion, with the exact number of points documented for each participant.

For participants presenting with both perineal pain and vulvar edema, the complete perineal pain protocol described above will be performed first. Subsequently, PBM will be applied to the edematous vulvar area using 808-nm infrared light at an energy density of 10 J/cm² for 10 s per point, with a 2-cm distance between adjacent application points. In addition, two irradiation points will be applied to the inguinal region, with 20 J/cm² per point, corresponding to 20 s per point, for a total of 40 J/cm² and 40 s in the inguinal region. The treatment sequence will therefore consist of perineal irradiation first, followed by irradiation of the edematous vulvar area and, finally, the two inguinal points, when vulvar edema is presente (Table 2).

**Table 2 Tab2:** Photobiomodulation intervention parameters for perineal pain and vulvar edema

Parameter	Perineal pain	Vulvar edema
Clinical condition	First- and/or second-degree perineal trauma + pain ≥ 3 on the NRS	Obstetric vulvar edema
Wavelength	808 nm (infrared)	808 nm (infrared)
Output power	100 mW	100 mW
Beam area	1 mm²	1 mm²
Power density	1.02 W/cm²	1.02 W/cm²
Application technique	Point-by-point	Point-by-point
Energy density	60 J/cm²	10 J/cm²
Application time	60 s per point	10 s per point
Energy per point	6 J	1 J
Number of points	1–2 points, according to lesion size	According to the extent of the edematous area
Application site	Around the lesion and along the course of the pudendal nerve	Over the edematous vulvar area
Distance between points	—	2 cm
Additional application	—	2 points in the inguinal region
Parameter for inguinal points	—	20 J/cm² per point
Application time at inguinal points	—	20 s per point
Energy at inguinal points	—	2 J per point
Total energy at inguinal points	—	4 J
Treatment sequence	Application around the lesion and along the pudendal nerve pathway	Edematous area → inguinal region

Note: For participants presenting with both perineal pain and vulvar edema, the perineal pain protocol will be performed first, followed by application to the edematous area and, subsequently, to the two inguinais points

Participants allocated to G2 will undergo the same application procedure, positioning, treatment sequence, and approximate treatment duration as participants in G1. However, the device will remain inactive, with no light emission, thereby providing a sham intervention. The same device and application sites will be used to maintain participant blinding. Participants in the sham group will also receive the same standardized postpartum education and usual care provided to the PBM group.

All intervention procedures will be performed by trained physiotherapists following a standardized operating procedure (SOP). The parameters, number and location of application points, duration, and energy delivered will be recorded for each participant to ensure treatment fidelity and reproducibility.

### Intervention modification and discontinuation

The intervention will be discontinued if participants report intolerable pain exceeding their pre-intervention Numeric Rating Scale (NRS) score, increased local tenderness accompanied by a sharp or stabbing sensation in the treated area, or any adverse event that may compromise participant safety. Participants may also withdraw from the study at any time without providing a reason. All withdrawals and their respective reasons will be documented and reported.

### Intervention adherence

Adherence will be monitored through attendance records and completion of all scheduled treatment sessions. A standardized checklist will be used to ensure protocol fidelity during each intervention session. Any protocol deviations will be documented. Because the intervention will be administered during hospitalization, an adherence rate of 90% is expected.

### Concomitant care

All participants will receive standard postpartum care, including guidance on perineal hygiene, posture, hydration, and activity modification. The use of analgesic medications will be permitted when clinically indicated and will be recorded in both groups to account for potential confounding factors.

### Recruitment

Participants will be recruited from the Pre-labor, Labor and Postpartum Unit (PPP), the Normal Birth Center (CPN), and the Surgical Ward of University Hospital. Recruitment will be conducted daily through active screening of medical records and direct contact by trained researchers.

### Participant characteristics and outcome assessments

Participants will undergo five assessments: three during the immediate postpartum period (baseline, immediately after the intervention, and 12 h after the intervention), one at 40 days postpartum, and one at 3 months postpartum. The schedule of assessments and assessment instruments is summarized in Table 3.

**Table 3 Tab3:** Detailed description of study outcomes

Outcome	Instrument/test	Description of the instrument/test	Scoring	Assessment timepoint	Clinically meaningful effect
Pain	Numeric Rating Scale (NRS)	A unidimensional instrument widely used to assess self-reported pain intensity.	0 (no pain) to 10 (worst pain imaginable).	T0, T1, and T2	Reduction of ≥ 2 points on the NRS.
	Digital pressure algometer	Assesses the pressure pain threshold in the bilateral peritraumatic region by applying gradually increasing pressure.	Value recorded in kgf/cm².	T0, T1, and T2	Increase in the pressure pain threshold.
Vulvar edema	Standardized photography and measuring tape	Objective assessment of vulvar edema using standardized photographic documentation and measurement of the edematous area.	Measurement in millimeters and photographic analysis.	T0, T1, and T2	Reduction in vulvar edema size.
Immediate postpartum functioning	Likert scale	Assesses difficulty in performing functional activities during the immediate postpartum period (standing up, sitting down, walking, and caring for the newborn).	1 = no difficulty to 5 = extreme difficulty.	T0, T1, and T2	Reduction in functional difficulty.
Patient satisfaction	Visual Analog Scale (VAS)	Assesses participant satisfaction with the treatment received.	0 = no satisfaction to 10 = maximum satisfaction.	T0 and T3	Increased satisfaction compared with the baseline assessment.
Global perceived change	Patient Global Impression of Change (PGIC)	Assesses the participant’s subjective perception of clinical improvement following the intervention.	1 = no change to 7 = very much improved.	T1 and T2	Score ≥ 5, indicating perceived improvement.
Late and remote postpartum functioning	World Health Organization Disability Assessment Schedule 2.0 (WHODAS 2.0)	Assesses functioning across six domains of daily life: cognition, mobility, self-care, getting along with others, life activities, and participation.	1 = no difficulty to 5 = extreme difficulty.	T3 and T4	Reduction in the total WHODAS 2.0 score.
Urinary incontinence	International Consultation on Incontinence Questionnaire–Short Form (ICIQ-SF)	Assesses the frequency and amount of urinary leakage and its impact on quality of life.	Total score ranging from 0 to 21.	T3 and T4	Reduction of approximately 2.5–5 points; changes of ≥ 4 points represent a clinically important improvement.
Sexual function	Female Sexual Function Index (FSFI)	Assesses sexual desire, arousal, lubrication, orgasm, satisfaction, and pain during the previous four weeks.	Total score ranging from 2 to 36; cutoff score = 26.55.	T4	Score > 26.55, indicating preserved sexual function.
Adverse events	Standardized clinical record	Assessment of intervention-related adverse events (increased pain, discomfort, skin irritation, hematoma, allergic reaction, or other complications).	Presence/absence; classified according to type and severity.	T1, T2, T3, and T4	Absence of serious treatment-related adverse events.

Legend *T0* pre-intervention, *T1* immediately after the intervention, *T2* 12 hours after the intervention, *T3* 40 days postpartum (late postpartum period), *T4* 3 months postpartum (remote postpartum period)

The baseline assessment will include the collection of sociodemographic and obstetric data, followed by a standardized physical examination. Perineal pain intensity will be assessed using the Numeric Rating Scale (NRS) and pressure algometry. The NRS is an 11-point scale ranging from 0 (no pain) to 10 (the worst pain imaginable), with pain categorized as mild (1–3), moderate (4–6), or severe (7–10). Pain intensity will be assessed using standardized verbal descriptors [18]. 

Pressure pain threshold will be measured using a calibrated MED.DOR^®^ digital pressure algometer, with readings expressed in kgf/cm². The device will be applied perpendicularly to the bilateral peritraumatic region, with one measurement obtained on each side. Participants will be instructed to indicate the moment when the sensation of pressure becomes painful by saying “stop,” and this value will be recorded as the pressure pain threshold. To ensure biosafety, the algometer probe will be covered with disposable plastic film and disinfected with 70% alcohol before each assessment [19].

The use of analgesic medication will be recorded at each assessment point, including the type of medication, dose, route of administration, and time elapsed between medication administration and pain assessment.

Vulvar Edema Area the area of vulvar edema will be quantified using digital image analysis with ImageJ software (National Institutes of Health, Bethesda, MD, USA). For each photograph, the edematous region will be manually outlined using either the Freehand Selection or Polygon Selection tool according to the anatomical boundaries of the edema. The software will automatically calculate the area of the region of interest (ROI). Images will be calibrated using a reference scale positioned in the same plane as the photographed area, allowing measurements to be expressed in square millimeters (mm²).

Participant satisfaction with the intervention will be assessed using a Visual Analog Scale (VAS) for satisfaction, ranging from 0 (no satisfaction) to 10 (maximum perceived satisfaction), administered at the final assessment [20]. 

Global perceived change will be assessed using the Global Perceived Effect Scale (GPE), which consists of seven response categories ranging from 1 (no change) to 7 (very much better). This outcome will be assessed immediately after the intervention and again 12 h later [21]. 

Immediate postpartum functioning will be evaluated using a 5-point Likert scale, assessing the level of difficulty in performing activities such as standing up, sitting down, walking, and caring for the newborn.

During the late and remote postpartum follow-up assessments, functioning will be evaluated using the World Health Organization Disability Assessment Schedule 2.0 (WHODAS 2.0), which assesses six domains: cognition, mobility, self-care, getting along with others, life activities, and participation. Responses are scored on a 5-point scale ranging from 1 (no difficulty) to 5 (extreme difficulty) [22]. 

Urinary incontinence will be investigated based on participants’ self-reported symptoms and the International Consultation on Incontinence Questionnaire–Short Form (ICIQ-SF), a validated instrument that evaluates the frequency, severity, and impact of urinary leakage on quality of life. Total scores range from 0 to 21, with higher scores indicating greater symptom severity and impact.

Sexual function will be assessed at 3 months postpartum using the Female Sexual Function Index (FSFI), which comprises 19 items distributed across the domains of desire, arousal, lubrication, orgasm, satisfaction, and pain. Total scores range from 2 to 36, with a cutoff score of ≤ 26.55 indicating possible female sexual dysfunction.

All study outcomes will be assessed by previously trained examiners who will remain blinded to participant allocation. The assessment instruments used in this study (NRS, pressure algometry, VAS for satisfaction, Global Perceived Effect Scale, WHODAS 2.0, ICIQ-SF, and FSFI) have demonstrated adequate psychometric properties, including validity and reliability, and are widely used in clinical research involving women during pregnancy and the postpartum period. 

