#### Inclusion criteria

Women will be eligible if they meet all of the following criteria: age > 15 years; pain intensity ≥ 3 on the Numeric Rating Scale (NRS); first- and/or second-degree perineal trauma and/or vulvar edema; immediate postpartum period (up to 12 h afterchildbirth) (Table 1).

**Table 1 Tab1:** Participant timeline: Schedule of enrollment, interventions, and assessments

	Trial period			
Timepointb	Enrollment	Post-randomization		Close-out
	July 2025 to December 2026 T0	Post-immediate postpartum T1	after 12 h T2	40 days, and 3 monthst T3,T4
ENROLLMENT:				
Eligibility screen	x			
Informed consent	x			
Randomization				
INTERVENTION/ COMPARATOR:				
G1 – Photobiomodulation	x			
G2 – Sham PBM + Usual care				
ASSESSMENTS:		x		
Pain (NRS)	x			
Vulvar edema	x	x	x	
Immediate postpartum functioning	x	x	x	
Patient satisfaction	x	x	x	
Patient Global Impression of Change (PGIC)	x	x	x	
ICIQ-SF				x
WHODAS 2.0				x
FSFI				x
Adverse events	x	x	x	x

Abbreviations *PBM* photobiomodulation, *T0* pre-intervention, *T1* immediately after the intervention, *T2* 12 hours after the intervention, *T3* 40 days postpartum, *T4* 3 months postpartum, *NRS* Numeric Rating Scale, *WHODAS 2.0* World Health Organization Disability Assessment Schedule 2.0, *ICIQ-SF* International Consultation on Incontinence Questionnaire–Short Form, *FSFI* Female Sexual Function Index

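### Satisfaction with treatment is judged against a rating taken before any treatment, and the scheduled visits do not agree

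*Protocol article*

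**What the plan says.** Patient satisfaction is one of the secondary objectives listed at the end of the Introduction. Three places in the protocol article define or schedule it.

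- **Table 3**, in the section on participant characteristics and outcome assessments. The description reads "Assesses participant satisfaction with the treatment received". Scoring is "0 = no satisfaction to 10 = maximum satisfaction". The timepoints are T0 and T3, and the entry for a clinically meaningful effect is "Increased satisfaction compared with the baseline assessment".
- **The text after Table 3**. The satisfaction VAS is "administered at the final assessment". No baseline rating is mentioned.
- **Table 1** (participant timeline). Marks stand at T0, T1 and T2, and the T3/T4 column is empty.

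The timing of T0 is not in doubt. The Table 3 legend reads "Legend *T0* pre-intervention, *T1* immediately after the intervention", and the Intervention section says "Before the intervention, participants will undergo the baseline assessment".

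A neighbouring outcome, global perceived change, has a smaller problem of the same kind. Table 3 gives T1 and T2, and the text agrees: "This outcome will be assessed immediately after the intervention and again 12 h later". Table 1 also marks T0. Tables 1 and 3 call the instrument PGIC; the text calls it the Global Perceived Effect Scale.

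**The concern.** A woman cannot rate a treatment she has not had. A T0 answer might reflect her expectations, her view of her obstetric care or the scale's default position, and the form cannot tell these apart. An increase from such an answer is not a measure of satisfaction with photobiomodulation, and both arms could meet the Table 3 criterion without any treatment effect.

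The visit conflict adds a second difficulty. Ratings at 12 hours, 40 days and 3 months are different quantities. Unless one visit is fixed beforehand, the visit and the handling of the T0 value may be chosen once data exist. The Statistical analysis section fits longitudinal outcomes with T0 as a level of time and treats the group × time interaction as the primary parameter. A T0 satisfaction rating, if collected, could therefore enter the estimated effect.

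**Working it through.** The plan gives no figure for this outcome, so the check is a comparison of statements.

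**Step 1: is the baseline term valid?** The Table 3 criterion needs change = VAS(T3) − VAS(T0). The construct is satisfaction with treatment already given. By the legend and the Intervention section, T0 comes before the only session. VAS(T0) therefore has no object, and the difference has no clear meaning for an individual woman or within an arm.

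**Step 2: do the schedules agree?**

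| Source | Satisfaction visits |
|---|---|
| Table 3 | T0, T3 |
| Text after Table 3 | final assessment only |
| Table 1 | T0, T1, T2 |

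The same section lists five assessments, the last at 3 months, so the plain reading of the final assessment is T4. No post-treatment visit is then shared by any two sources. Other readings do not remove the conflict:

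- If it means the last in-hospital assessment (T2), the text agrees with Table 1 on that visit but not with Table 3.
- If it means T3, the text agrees with Table 3 on the post-treatment visit but still omits T0.

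On every reading the text collects no T0 value, so the Table 3 criterion could not be calculated from data collected as the text describes.

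**Step 3: does this rest on Table 1?** No. Steps 1 and 2 stand on Table 3, its legend, the Intervention section and the text. Table 1 adds a third version. Its satisfaction row has the same pattern as the vulvar edema and immediate functioning rows, whose T0 to T2 marks match Table 3, but other rows look displaced.

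**Step 4: what does the T0 rating do to the comparison between arms?** If it is given before treatment and without knowledge of allocation, its expected value is the same in both randomized arms. Subtracting it does not bias the between-arm difference; it changes the precision and obscures the meaning. With equal variances σ² and correlation ρ between the two ratings, Var(change) = 2σ²(1 − ρ). That is 2σ² at ρ = 0 and σ² at ρ = 0.5. The documents give neither σ nor ρ for satisfaction, so the loss cannot be sized.

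**The case against.** The strongest reply is that the protocol already contains a workable version. The text describes a single VAS with no baseline, the Statistical analysis section reports mean differences with 95% CI, and the Table 3 wording sits in a column on clinical meaning rather than in an analysis rule. This is largely right. A reader might infer that satisfaction cannot be measured in this trial at all. The documents do not support that: a post-treatment score compared between arms is measurable. What fails is the increase over baseline and the absence of one agreed visit.

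A reader might also want to attach a power loss. That would mean borrowing the standardized effect of 0.784 assumed for pain in the sample size section and choosing a correlation. Neither belongs to satisfaction. Nor should the 20% dropout be counted as a further loss on top of 27 per arm: the plan inflates 54 to 68 for it, and 68 × 0.80 = 54.4, so 27 per arm is already the number after dropout.

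The case against relying on Table 1 also stands in part. A mark appears on the line headed for assessments, pain is marked only at T0, and the randomization and sham rows are empty. The T0 column also holds the photobiomodulation mark and an adverse-event mark that Table 3 does not list at T0, so a mark there need not mean before treatment. The perceived-change mark at T0 rests on this table alone. The two instrument names are clerical, since the visits and the 1 to 7 range agree between Table 3 and the text.

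**Conclusion.** The point holds for Table 3 and for the schedule. The stated criterion uses a pre-treatment rating of treatment not yet received, and Table 3 and the text cannot both be followed. Table 1 is supporting evidence only.

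The size is modest: one secondary outcome, with no effect on the primary pain analysis or the sample size, and no defensible power figure. The conclusion assumes that T0 means what the legend says and that the Table 3 entry is intended as the criterion by which satisfaction will be read. The change is worth making because it is cheap and turns an uninterpretable change score into a plain randomized comparison.

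**What to change.** 1. Remove the T0 satisfaction rating from Table 3 and, if the mark is in the published table, from Table 1.
2. Replace the comparison with baseline by a comparison of photobiomodulation with sham: mean difference in VAS score with 95% CI, no baseline term.
3. Name one post-treatment visit, delete the others, and state it identically in Table 1, Table 3 and the outcome text. T2 is one option and has the least exposure to loss to follow-up; Table 3 at present points to T3 and the text, on its plain reading, to T4. The sponsor should choose and give the reason.
4. Remove the perceived-change mark at T0 in Table 1 if it is in the published table, and use one instrument name throughout.

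The cost is edits to two tables, the text and the case report form, with one item fewer at T0. Table 1 dates enrolment from July 2025, so some women may already have passed the chosen visit without a rating. The change should therefore be documented and sent to the registry, as the Protocol amendments section requires, and any ratings missing for this reason should be reported by arm.

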### Statistical analysis

Statistical analyses will be performed using the Statistical Package for the Social Sciences (SPSS), version 20.0 (IBM Corp., Armonk, NY, USA), adopting a significance level of 5% (*p* < 0.05). Descriptive statistics will be presented as absolute and relative frequencies for categorical variables and as means, standard deviations (SD), and 95% confidence intervals (95% CI) for continuous variables.

The primary analysis of longitudinal outcomes will be performed using linear mixed-effects models. Treatment group (photobiomodulation and sham), time (T0: baseline; T1: immediately after the intervention; T2: 12 h after the intervention; T3: 40 days postpartum; and T4: 3 months postpartum), and the group × time interaction will be included as fixed effects, while participant will be included as a random effect to account for the correlation among repeated measurements within the same participant. The group × time interaction will be considered the primary parameter for determining whether changes in outcomes over time differ between the photobiomodulation and sham groups. Baseline outcome values will be included in the model when appropriate.

Model assumptions will be assessed by examining the distribution of residuals and the homogeneity of variance. If substantial deviations from model assumptions are identified, appropriate data transformations or alternative statistical approaches will be considered.

For baseline comparisons, categorical variables will be analyzed using Pearson’s chi-square test or Fisher’s exact test, as appropriate. Continuous variables will be analyzed using the independent-samples Student’s t-test for approximately normally distributed data or the Mann–Whitney U test for non-normally distributed data.

When a significant group × time interaction is identified, post-hoc pairwise comparisons will be performed to determine differences between groups at each assessment time point and changes within each group over time. The Bonferroni correction will be applied to adjust for multiple comparisons and control the family-wise type I error rate.

The magnitude of the intervention effect will be estimated using mean differences (MD) for continuous outcomes and relative risks (RR) for dichotomous outcomes, with corresponding 95% confidence intervals (95% CI). The number needed to treat for benefit (NNTB) will be calculated for dichotomous outcomes when applicable.

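### Table 3 defines the meaningful effect on ICIQ-SF and WHODAS 2.0 as a reduction, but neither has a pre-treatment value, and the ICIQ-SF cell gives two figures that are not equivalent

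*Protocol article*

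**What the plan says.** Table 3 (Participant characteristics and outcome assessments) has a column for the clinically meaningful effect.

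- **ICIQ-SF:** the entry is "Reduction of approximately 2.5–5 points; changes of ≥ 4 points represent a clinically important improvement". The scoring and timing cells read "Total score ranging from 0 to 21. T3 and T4". The text below the table confirms the direction: "Total scores range from 0 to 21, with higher scores indicating greater symptom severity and impact".
- **WHODAS 2.0:** the entry is "Reduction in the total WHODAS 2.0 score", also at T3 and T4, with no cut-off.
- **Visits:** T3 is 40 days and T4 is 3 months postpartum. Table 1 marks both instruments in that late column only.
- **Treatment:** "A single treatment session will be performed during the immediate postpartum period, within 12 h after childbirth". Both late visits therefore follow treatment.
- **Eligibility:** the criteria are age, pain score, "first- and/or second-degree perineal trauma and/or vulvar edema; immediate postpartum period (up to 12 h afterchildbirth". Neither incontinence nor disability is required at entry.

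The Statistical analysis section makes the group × time interaction the primary parameter for longitudinal outcomes. It places comparisons between arms at each visit after a significant interaction. It promises mean differences for continuous outcomes and "relative risks (RR) for dichotomous outcomes, with corresponding 95% confidence intervals (95% CI"), with a number needed to treat where applicable. It does not name the dichotomous outcomes.

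**The concern.** A reduction needs a starting point. For pain on the NRS there is one, because T0 precedes treatment. For sexual function none is needed, because the FSFI criterion is a level at T4. The ICIQ-SF and WHODAS 2.0 cells use the language of change without any reading before treatment, and they do not say which visit the change is counted from.

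If the change is taken within a woman, it can only be T3 minus T4. Any benefit already present at day 40 is then invisible, or counts against the arm that has it, because a low score at T3 leaves little room to fall. The interaction shares this blind spot, since with two visits it is the between-arm difference in that same change.

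Separately, the ICIQ-SF cell offers about 2.5–5 points and at least 4 points without saying which governs. The choice could therefore be made after the data are seen.

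**Working it through.** The plan has no calculation of its own for these outcomes, so there is no figure to reproduce.

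**1. Which change is available.** The readings are T3 and T4 only. The within-woman reduction is score(T3) − score(T4), and both follow treatment.

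**2. The two ICIQ-SF figures, by size of fall (whole-number scores, 0 to 21).**

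| Fall from T3 to T4 | At least 2.5 | 2.5 to 5 as a literal range | At least 4 |
|---|---|---|---|
| 0, 1 or 2 | no | no | no |
| 3 | yes | yes | no |
| 4 or 5 | yes | yes | yes |
| 6 or more | yes | no | yes |

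The firm disagreement is at a fall of 3. The disagreement at 6 or more exists only if 5 is read as a ceiling.

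**3. Example women.**

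- Scores 0 then 0: fall 0, meets neither figure.
- T3 score of 2 or less: the largest possible fall is 2, so she can never meet either.
- Scores 8 then 3 in the sham arm: fall 5, meets both.
- Scores 7 then 4: fall 3, depends on which figure is used.

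**4. If the figures were used to classify women (not stated in the protocol).** Let p be the proportion leaking at T3 and q the proportion of those women whose fall meets the threshold. The share qualifying is p × q, so

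RR = (p_PBM × q_PBM) / (p_sham × q_sham).

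With equal q this reduces to p_PBM / p_sham. All values of p below are assumptions:

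- 15% against 30%: RR = 0.50
- 20% against 30%: RR = 0.67
- 30% against 30%: RR = 1.00

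An RR below 1 here means fewer PBM women qualify although fewer leak. With 15% against 30%, q_PBM would have to be twice q_sham (0.30 / 0.15 = 2) merely to bring the RR to 1.

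**5. Effect of the choice of figure.** Two simulations assumed 30% leakage in the sham arm at T3.

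| Assumed scores in women who leak | At least 4 | At least 2.5 |
|---|---|---|
| T3 mean 8, SD 3; half improve by T4 | 10.6% | 12.9% |
| T3 mean 9, SD 3; mean fall 4, SD 2.5 | 16.9% | 21.5% |

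In an arm of 34 with full follow-up, the gap is 34 × 0.023 = 0.8 women in the first case and 34 × 0.046 = 1.6 in the second.

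**6. The interaction.** Suppose mean scores are 2 then 1 with PBM and 6 then 5 with sham. The arms differ by −4 at T3 and −4 at T4. The interaction is (1 − 2) − (5 − 6) = 0, so the comparisons by visit would not be triggered.

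**7. Could either figure judge the difference between arm means?** With 30% of sham women leaking at a mean of about 8, the sham mean over all women is 0.30 × 8 = 2.4. Abolishing leakage completely would give a difference of 2.4, below both 2.5 and 4. With 40% leaking at a mean of 9 the ceiling is 0.40 × 9 = 3.6, still below 4. A within-woman threshold is not a usable pass mark for a mean difference that includes the many women who score 0.

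**The case against.** **No responder analysis is specified.** A reader might infer that each woman will be scored a success or failure on the ICIQ-SF. The documents do not support that. The column is an interpretive benchmark, a 0–21 score fits naturally under mean differences, and the relative-risk sentence names no outcome. This stands, so the reversed relative risk is conditional.

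**Reduction could mean a lower PBM than sham mean at T3 or T4.** The data allow this reading and it matches the planned mean difference, which is not itself made conditional on the interaction. It stands as a possibility, although the words changes and improvement in the ICIQ-SF cell lean towards change within a woman. If the between-arm reading is meant, the table should say so.

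**The two figures do not flatly contradict each other.** Four lies inside 2.5–5, and treating 5 as a ceiling would be strained. This stands, and what remains is the ambiguity at a fall of 3.

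**The relative risks carry no evidence.** They return the assumed ratio of T3 incontinence. With equal leakage the RR is 1.0, and if PBM sped recovery after day 40 the same rule could favour PBM. A reader should not infer that the trial will be biased towards sham.

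**The WHODAS 2.0 cell has no cut-off.** It cannot classify anyone, so only the missing starting point applies to it.

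**These are secondary outcomes.** The Discussion already warns against reading the late outcomes as direct evidence of a long-term effect, and an unseen analysis plan may define responders. Both points lower the stakes. Neither repairs a criterion that Table 3 prints and that does not fit the visit schedule, and the Expected outcomes section still anticipates improvement in urinary incontinence.

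**Conclusion.** The point holds in a limited form. For ICIQ-SF and WHODAS 2.0, Table 3 states a reduction where no pre-treatment value exists. Read within a woman, it can only be the change from day 40 to month 3, which cannot show leakage or disability prevented before day 40. Tying comparisons by visit to a significant interaction does not make up for this, because a constant difference between arms gives an interaction of zero. The ICIQ-SF cell also prints two non-equivalent figures.

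These conclusions follow from the table and schedule alone and need no assumption. The size does need assumptions: the documents give no incontinence prevalence, score distribution or recovery rate. The relative risks of 0.50 and 0.67 illustrate direction only. They require that women be classified on the ICIQ-SF figures, that PBM lower leakage at day 40, and that later recovery be equal in the arms. The pain comparison and its sample size are unaffected.

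**What to change.** - **Table 3, ICIQ-SF and WHODAS 2.0:** define the effect as the PBM-versus-sham difference in score at T3 and at T4.
- **Statistical analysis:** add one sentence saying that these two differences, with 95% confidence intervals, are estimated whether or not the group × time interaction is significant.
- **Dichotomous incontinence outcome, if one is reported:** define it as a status at each visit, for example an ICIQ-SF score above 0, with a relative risk at T3 and at T4. Do not define it as a fall from T3 to T4. The protocol also collects self-reported leakage, so it should say which source defines the status.
- **ICIQ-SF threshold:** keep one figure, label it as a within-woman change given for context, and do not use it as the pass mark for the difference between arm means.

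The cost is wording in two table cells and one sentence of analysis text. No new data, visits or participants are needed. Because the definition of an outcome changes, the protocol's own amendment procedure, including notice to the registry, would apply, and the change should be dated before analysts see allocation. The downside is that the summary of improvement within women is dropped or becomes descriptive.
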